### Outcome assessment

This study will run for 12 weeks and cognitive function will be assessed by neuropsychological measurement scales which include Mini–mental state examination (MMSE), Montreal Cognitive Assessment (MoCA), Functional Independence Measure Scale (FIM) at baseline and again at 4, 8 and 12 weeks (within a time window: +/- 3 days). All outcomes will be measured by several experienced assessors who are blinded to the randomization group after the baseline visit in the Evaluation Department of Rehabilitation Hospital Affiliated to FJTCM.

### Primary outcomes

#### Mini–mental state examination (MMSE)

The mini–mental state examination (MMSE) or Folstein test [49] is a brief 30-point questionnaire test that is used to screen for cognitive impairment. MMSE includes items to evaluate spatial and temporal orientation, short-term memory, attention and calculation abilities, language, thinking, and action planning. MMSE will take about 15 to 20 minutes. In this study we use the Chinese version of MMSE [42] to follow the course of cognitive changes in an individual over time, thus making it an effective way to document an individual’s response to treatment.

### Secondary outcomes

#### Montreal cognitive assessment (MoCA)

The MoCA [50] test is a one-page 30-point test administered in approximately 10 minutes assesses several cognitive domains: visual-executive, naming, attention, language, abstraction, delayed recall, and orientation. It makes up the shortcoming of MMSE to have a comprehensive evaluation on the cognitive changes in the patients with different degrees of cognitive impairment. We use the Beijing version 26 August, 2006 translated by Wei Wang & Hengge Xie [51].

#### Functional independence measure scale (FIM)

The FIM [52] is a detailed measurement of functionality tool used to evaluate the functional status of patients throughout the rehabilitation process following a stroke [53]. The FIM’s assessment (We use the Chinese version translated by Yulong Wang [42]) of degree of disability depends on the patient’s score in 18 categories, focusing on motor and cognitive function which may reflect global cognitive function [54]. So, FIM scores may be interpreted to indicate level of independence or level of burden of care.

### Patient safety

Adverse effects attributable to the RehaCom therapy may include mental fatigue or headache. Symptoms usually resolve in patients as they progress with therapy and become more familiar with it [33]. Acupuncture may cause discomfort or bruising at the sites of needle insertion, nausea, or feeling faint after each treatment.

During the trial, all unexpected adverse events (AEs) will be observed in detail and documented in CRFs. All AEs reported should be analyzed regardless of the investigators’ assessments of causality. If serious adverse events happen, the researchers should report to the PL and ethics committee immediately, who will make a decision on whether the participant needs to withdraw from the study.

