**Method/Design:**

A randomized controlled trial of 2 × 2 factorial design will be conducted in the Rehabilitation Hospital Affiliated to Fujian University of Traditional Chinese Medicine. A total of 240 patients with cognitive dysfunction after stroke who meet the eligibility criteria will be recruited and randomized into RehaCom training group, acupuncture group, a combination of both or control group in a 1:1:1:1 ratio. All patients will receive conventional treatment. The interventions will last for 12 weeks (30 min per day, Monday to Friday every week). Evaluations will be conducted by blinded assessors at baseline and again at 4, 8 and 12 weeks. Outcome measurements include mini–mental state examination (MMSE), Montreal cognitive assessments (MoCA), functional independence measure scale (FIM) and adverse events.

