**Table 1 Tab1:** **Trial processes chart**

Items	Before enrollment	Intervention period 1	Outcome assessment 1	Intervention period 2	Outcome assessment 2	Intervention period 3	Outcome assessment 3
	-2-1(week)	1-4(week)	5(week)	5-8(week)	9(week)	9-12(week)	13(week)
Inclusion criteria	×						
Exclusion criteria	×						
Informed consent	×						
Baseline	×						
Randomization and allocation	×						
Intervention		×		×		×	
Mini-mental status examination	×		×		×		×
Montreal cognitive assessment	×		×		×		×
Functional independence measure scale	×		×		×		×
Adverse events		×		×		×	
Reasons of drop-out and withdrawals		×		×		×	

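### The adverse-event recording rule is limited to unexpected events, which conflicts with the unrestricted adverse-event outcome and, read literally, could leave known non-serious reactions unrecorded, mainly in the active arms

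*Protocol article*

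**What the plan says.** The Patient safety section of the protocol article opens with the reactions that can be foreseen. For the computer training: "Adverse effects attributable to the RehaCom therapy may include mental fatigue or headache". For needling: "Acupuncture may cause discomfort or bruising at the sites of needle insertion, nausea, or feeling faint after each treatment". The next paragraph says what goes into the case report form: "During the trial, all unexpected adverse events (AEs) will be observed in detail and documented in CRFs". It continues: "All AEs reported should be analyzed regardless of the investigators", the sentence ending with a reference to their causality assessments. Serious events have a separate route: "If serious adverse events happen, the researchers should report to the PL and ethics committee immediately".

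Two other places describe adverse events without the word *unexpected*. The abstract (Method/Design) ends its list of outcome measurements with "functional independence measure scale (FIM) and adverse events". Table 1 has a row "Adverse events" marked in all three intervention periods. The same table has a row for reasons for drop-out and withdrawal, marked in the same three periods.

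**The concern.** A reaction that the protocol has just foretold is, in the ordinary sense of the word, expected. A recording rule that speaks of unexpected events does not cover it. This is a stated rule, not detail left to a fuller document, and it differs from the scope of the outcome given elsewhere in the same article. Later analysis cannot repair the gap, because an analysis plan cannot count events that were never written down.

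What is at stake is the comparison of adverse events between the arms. The foreseeable reactions are listed only for the two active interventions, so a filter on expectedness does not act equally on the four groups. According to the Blinding and Quality control sections, patients, therapists and investigators know the allocation, so whether an event counts as expected can be judged with the arm in view.

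**Working it through.** No arithmetic reproduces or refutes a figure here, because the plan gives none for adverse events. The check is to set the statements side by side.

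**Step 1. What each statement covers.**

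| Place | What it governs | Limited to unexpected events? |
|---|---|---|
| Abstract, Method/Design | Adverse events as an outcome | No |
| Table 1 | When adverse events are collected | No |
| Patient safety, recording sentence | What is documented in the CRF | Yes |
| Patient safety, analysis sentence | Which reported events are analysed | No limit by causality; silent on expectedness |
| Patient safety, serious events | Reporting to the project leader and ethics committee | No |
| Table 1, drop-out row | Reasons for leaving | No |

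The Quality control section mentions serious adverse events only as a topic for investigator meetings. No statement says that expected, non-serious events are to be entered in the CRF.

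**Step 2. Does the analysis sentence widen the rule?** It removes a filter on causality at the analysis stage, and it applies to events already reported. A filter on expectedness acts earlier, at recording, and is left untouched.

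**Step 3. Which arms would lose events under a literal reading?** The section names two reactions for RehaCom (fatigue, headache) and four for acupuncture (discomfort, bruising, nausea, faintness).

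| Arm | Foreseeable reactions named |
|---|---|
| Control (CG) | 0 |
| RehaCom (EG1) | 2 |
| Acupuncture (EG2) | 4 |
| Combination (EG3) | 2 + 4 = 6 |

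With 60 patients per arm, the list touches 3 × 60 = 180 of 240 patients and none of the 60 controls.

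**Step 4. Direction of the bias.** Take a non-serious headache. In control or acupuncture-only patients it is on no list for their treatment and would be recorded. In RehaCom or combination patients it is on the list and could be left out. Nausea behaves the same way for acupuncture: recordable in control and RehaCom-only patients, open to omission in acupuncture and combination patients. In each case the arms that receive the intervention are the ones that could lose events, so the contrast moves towards no harm. The combination arm, where the needles stay in during training, is exposed to both omissions.

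**Step 5. What is not lost.** Serious events are reported whether or not they were foreseeable. A reaction that makes a patient stop should appear in the drop-out row. What remains at risk is the reaction that is known, non-serious and tolerated.

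**The case against.** The strongest reply is that the article never says that *only* unexpected events are recorded. It says that all unexpected ones are, which does not expressly exclude the others. It does not define the term, does not call the listed reactions expected, and is loosely worded in many places, so *unexpected* may simply stand for *untoward*. Table 1 and the abstract, both unrestricted, suggest that wider collection was meant. All of this stands. A reader might infer that the trial has decided to filter out known harms and that the adverse-event comparison is therefore biased; the documents do not support so firm a statement. They support a conflict between passages and a conditional consequence.

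A reader might also try to give the problem a size from planned exposure, 12 weeks × 5 days = 60 sessions per patient. That counts scheduled sessions at full attendance, not lost events, and the article gives no reaction rates to convert one into the other.

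It is also fair to say that adverse events are absent from the primary and secondary outcome sections and that both stated aims concern effectiveness. That lowers the weight of the point but does not remove it, since the abstract names adverse events as an outcome measurement.

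The reply does not remove the inconsistency. Staff who fill in forms may follow the written rule, and the one sentence on CRF content carries the limit.

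**Conclusion.** The point holds as an inconsistency with a conditional effect. The recording rule in the Patient safety section is narrower than the outcome in the abstract and the schedule in Table 1. If staff apply the rule literally and treat the listed reactions as expected, non-serious known reactions may go unrecorded, mainly in the three active arms, and the between-arm comparison of adverse events would lean towards no harm. If staff read the word loosely and follow Table 1, there is no loss.

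The size cannot be stated, because it depends on reaction rates and on staff practice, neither of which the article gives. Serious events, reasons for withdrawal and the MMSE analysis are outside the problem. It should be corrected because a named outcome depends on it and the correction is simple.

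**What to change.** Reconcile the passages. In the Patient safety section, replace the reference to all unexpected adverse events with: *all adverse events, expected or unexpected, in all four arms*. The recording rule then matches the abstract and Table 1.

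State that these events are recorded during the intervention periods that Table 1 already marks, by staff who do not assess outcomes. Questions about bruising or needle-site discomfort at an assessment visit could reveal the allocation to the blinded assessors.

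The cost is a short change of wording and slightly more data entry. Sample size, visits and the efficacy analysis do not change.

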### Data collection and management

Having sought consent, the demographic and baseline characteristic data in CRFs will be completed by a specific RA who is masked to treatment allocation and trained to administer questionnaires in a standardized way.

The data consists [55] of demographic details, review of medical history and medication, the lesion, affected side, handedness, cognitive function, time since stroke, stroke type and subtype, rehabilitation history (treatments until study start), details of current and cognitive treatment received within the previous 3 months and concomitant medications are recorded. Data will be obtained by direct questions to patients, from medical records, and from a relative or proxy.

Outcome measurement will be measured by the outcome assessors after the intervention. RAs will conduct quality control of data collection and be responsible for data entry. The PL will be responsible for initial data cleaning, identifying, coding, and conversion into the proper format for data analysis.

All forms must be dated and signed by the responsible investigator or one of his/her authorized staff members.

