### Participant and recruitment

We will recruit 240 eligible patients from the Rehabilitation Hospital Affiliated to FJTCM who suffer from cognitive disorders caused by stroke with age above 18 years. The eligible patients must meet the following inclusion criteria as well as the exclusion criteria. A CONSORT diagram of participant recruitment is shown in Table 1. Patients will be recruited as inpatients or from the outpatient therapy department of the rehabilitation hospital by their treating therapist, through an advertisement at the hospital’s homepage, and through flyers at several locations of the hospital. Interested patients can contact the project leader (PL) through their therapist, by phone, email, or mail. If an applicant meets the study criteria, he or she will be invited to the research.

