### Quality control

A trained RA will explain to each participant the nature of the study, its purpose, the procedures involved, the expected duration, the potential risks and benefits and any discomfort it may entail. Patients or their legal guardians will receive an information letter about the study and there will be no time limit for them to consider implications, ask questions, and respond to the invitation to participate. Participants will be informed that they are free to withdraw from the treatment under study at any stage for any reason without any consequences.The participants screening must according to the inclusion and exclusion criteria. If they meet the inclusion criteria and not meet the exclusion criteria, this procedure will pass. On the contrary, the disqualified participants will be excluded, and the researchers will record the number and the reasons.The random allocation sequence will be produced by an independent statistician via the statistical software SAS 9.1. The project manager allocates the participants according to the random allocation sequence, and it must be deposited for safe keeping ensuring nobody else knows. The cessation of blinding will take place only after all the trial is completed.The missing data should not appear in the CRFs of the missing data in principle. If any missing data appears, researchers should find out whether it is missed in the raw data. If it is missed when loading into database, it should be reloaded. If the missing data affects outcome measure, the participant will be rejected.To ensure that treatments are of a high standard and delivered in accordance with the trial protocol, clinicians involved in assessments, treatment or training will have to provide proven record of at least three year of clinical experience and certified training or education in related fields of rehabilitation or research. The needling will only be performed by professional physicians with specific training in TCM and a minimum of five years of experience. They will participate in a two-day training in the standard operating procedures (SOPs) provided by the author of the manualized protocol and the standard operation videos. In this training the protocol will be explained and practiced on each other during exercises and role-plays. The therapist in the control condition will receive no extra training. In addition, all treatments provided to patients will be carefully recorded in the CRFs.Blinding of study personnel in research projects is a main quality criterion of a study [43]. Although patients, investigators, and therapists administering treatment will not be blinded, those assessing the patients for primary and secondary endpoints will be blinded to patient treatment assignment. The investigators, therapists and assessors are different people. Patients will be told not to talk to the examiner about the group allocation or therapy content during the post-intervention assessments.To maintain the quality of this trial, monitoring will be conducted by the PL located in the Rehabilitation Hospital Affiliated to FJTCM. Investigators can also be convened to discuss practical issues that might be encountered, such as dealing with serious adverse events, revising the protocol, and addressing certain important issues that might be raised by investigators and participants.

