The biggest limitation of this protocol is that it is not double-blinded. However, the outcome assessors and statistical analysts will be blind to the intervention to decrease possible bias to ensure the quality of this trial. The study also lacks long-term follow-up and evaluation. The 12-week intervention period reflects what is done in actual clinical practice and is long enough to test whether a rehabilitation modality is effective in the short term and whether the efficacy is sustained during the follow-up period.

In conclusion, the results of this trial are expected to clarify the synergistic effect of acupuncture and RehaCom cognitive training on cognitive dysfunction after stroke. Furthermore, to confirm whether combined or alone of acupuncture and RehaCom cognitive training, are more effective than conventional treatment in the management of post-stroke cognitive dysfunction.

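### Outcome data are cleaned and coded by the project leader, who is not stated to be masked, at a step that lies outside the blinding of assessors and analysts

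*Protocol article*

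**What the plan says.** The Discussion names the absence of double-blinding as the main limitation and offers this in answer: "the outcome assessors and statistical analysts will be blind to the intervention to decrease possible bias". The Blinding section supports it. A specified research assistant (RA) holds the sequence and the code, the groups are relabelled A to D, and the code is opened only after the analysis.

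Data collection and management divides the data work. On entry and checking: "RAs will conduct quality control of data collection and be responsible for data entry". On what follows: "The PL will be responsible for initial data cleaning, identifying, coding, and conversion into the proper format for data analysis".

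The PL has other duties. Under Quality control, "monitoring will be conducted by the PL located in the Rehabilitation Hospital Affiliated to FJTCM". Under Patient safety, "If serious adverse events happen, the researchers should report to the PL and ethics committee immediately", and the same sentence leaves the decision on withdrawal to them. Under Participant and recruitment, the PL is a point of contact: "Interested patients can contact the project leader (PL) through their therapist, by phone, email, or mail".

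On who is not masked, Quality control says "Although patients, investigators, and therapists administering treatment will not be blinded", and goes on to state that the endpoint assessors are. The PL is not named in either group.

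**The concern.** The scores are produced by blinded raters and analysed by a blinded analyst, but they pass through a third person on the way. If that person can learn the arm, decisions about doubtful or incomplete scores can be influenced by it, and neither the raters nor the analyst would notice. The trial is open to patients and therapists, and its authors state in the Background a firm expectation that the combination will do more than the sum of its parts. The primary aim is an interaction on the MMSE, a contrast of four arm means, so any selective handling of scores in one arm passes directly into it.

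**Working it through.** The article gives no figure for this point. The main check is to set the sections side by side.

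1. **Is the PL masked anywhere?** No. The article describes masking role by role: the RA who collects baseline data (Data collection and management), the assessors (Outcome assessment, Quality control) and the analysts (Discussion). The separation of duties under Blinding covers the RA, therapists, assessors and analyst. The PL appears in none of these.
2. **Is there a route by which the PL could learn the arm?** Yes. Treatment allocation and Quality control both have the treatments given recorded in the case report forms. Patient safety has adverse events recorded there too, and the expected ones differ by intervention: needle-site bruising for acupuncture, mental fatigue or headache for RehaCom. Someone cleaning the full record would see these fields. An A–D label does not hide the arm from a person who can read the treatment field. No separation of outcome from treatment records is described. Monitoring and serious-event reports are further routes.
3. **Is there room for judgement at this step?** Some. Quality control says that a participant is rejected if missing data affect an outcome measure, and does not say who decides. Statistical analysis says that all allocated subjects are analysed with available data. The two are not reconciled, so a participant's inclusion may turn on a decision made while the data are handled.

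**Illustration of size.** Inputs from Sample size: mean MMSE improvements of 2.7 (control), 5.9 (RehaCom, EG1), 3.7 (acupuncture, EG2) and 6 (combination, EG3); SD 5.2; about 50 per arm before dropout inflation.

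- Implied interaction: 6 − 5.9 − 3.7 + 2.7 = −0.9.
- Its standard error at 50 per arm: √(4 × 5.2²/50) = 2 × 5.2/√50 = 1.47.
- Shift in an arm mean when m of 50 values lying 1 SD below it are dropped: m × 5.2/(50 − m).
  - m = 3: 15.6/47 = 0.33, or 0.33/1.47 ≈ 0.23 standard errors.
  - m = 5: 26/45 = 0.58, or 0.58/1.47 ≈ 0.39 standard errors.

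EG3 enters the interaction with weight +1, so the interaction moves by the same amount: from −0.9 to about −0.57 or −0.32. The values of m and the 1 SD distance are assumptions, not figures from the article.

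**The case against.** The strongest reply is that a journal article need not describe data management. Masked cleaning, query rules and database lock usually sit in a full protocol or data management plan, and neither is shown. That stands for the lock and the query rules, whose absence is not the finding. It does not dispose of the point, because the article expressly gives cleaning and coding to the PL, in the same section that states the masking of the baseline RA.

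Several stronger readings are tempting, and the documents do not support them:

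- *The blinding is broken.* It is not. Assessors still score masked, and the analyst still works under the A–D code. Cleaning by the PL unmasks neither.
- *The PL knows the allocation.* This is never stated. Investigators are listed as unblinded, but the PL is not named. The sequence is placed with an RA (Blinding) or with the project manager (Quality control), and nothing says that the project manager and the PL are the same person.
- *The PL recruits, and so knows the arms.* The PL is only a contact point before randomization. Recruitment is by therapists, advertisement and flyers.
- *The PL controls all data handling or may exclude patients.* RAs do the entry and quality control, and no sentence gives the PL power to exclude.
- *A 0.33 shift swamps the planned effect of 0.1.* The 0.1 is the simple difference EG3 − EG1 (6 − 5.9). The relevant quantity is the interaction, −0.9, and against its standard error the shift is modest.

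**Conclusion.** The point holds as an avoidable weakness in the assignment of duties. A person with monitoring and safety roles, not stated to be masked, cleans and codes the outcome data between two masked parties, from forms that record treatment. This rests on two readings: that cleaning is done on the case report form data as described, and that no unseen document strips out the treatment fields. If such a document exists, the remedy is one clarifying sentence.

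The likely size of any bias cannot be derived from the article. The illustrated shift of 0.33 is a little over a third of the implied planning interaction (0.33/0.9 = 0.37) but under a quarter of its standard error. That supports correcting the assignment. It does not support saying that the results would be invalid.

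**What to change.** In Data collection and management, reassign outcome cleaning, query decisions and coding to the blinded analyst described under Blinding. The analyst should work on MMSE, MoCA and FIM records without treatment, adverse-event or arm fields. The PL then only answers queries about source records. Keep a log of every changed score and every exclusion, with the reason, and lock the outcome file before the A–D codes are attached.

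The task should not go to the statistician who generates the allocation sequence. That person is the source of the allocation and is stated, under Randomization and allocation, not to be involved in the study.

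The cost is slightly slower query resolution and the upkeep of a log. No extra patients, visits or staff are needed, and since Trial status reports recruitment as ongoing, the change can be made before analysis.
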